#### Brain scanning

A 7-Tesla MRI machine, located at RRI in London, ON, will be used to gather magnetic resonance spectroscopy (MRS), functional, and structural data of the hippocampi and the posterior cingulate cortices (PCCs), as well as fronto-striatal connectivity at the resting state. During the scanning session, instructions will be presented to the participant through MRI-compatible headphones. The scanning session will include: a three-dimensional Magnetization Prepared Rapid Acquisition Gradient Echo (MPRAGE) scan for structural measurements; 8 min of a T2 (echo planar imaging (EPI))-sequence during the eyes-open resting state; and a MRS from the hippocampal and PCC voxels collecting using simplified localization by adiabatic selecting refocusing (semi-LASER), in line with a previously established MRS protocol [72]. MRS will be used to measure levels of glutathione (GSH). Given the time for equipment set-up and scanning, scanning procedures are expected to take close to 1 h for completion.

#### Magnetic Resonance Environment Screening Form

This is a Western University Centre for Functional and Metabolic Mapping questionnaire that participants need to complete if they wish to participate in the MRI portion of this study. It surveys surgical history as well as the presence of medical implants that may be impacted by MRI scanning (e.g., pacemakers) or otherwise problematic implants (e.g., metal implants).

#### Falls Efficacy Scale – International (FES-I)

The FES-I is a 16-item, self-rated scale used to assess fear of falling. Participants are asked about their fear of falling while doing various daily tasks (e.g., “Going up or down stairs”) and rate items on a scale of 1 (“Not concerned at all”) to 4 (“Very concerned”). Scores range from 16 to 64, with higher scores indicating greater fear of falling [73].

#### Gait

Outcomes include mean stride length and mean gait velocity. Both stride length and gait speed will be measured using a GAITRite® portable walkway (CIR Systems Inc., Franklin, NJ, USA). This device utilizes embedded pressure sensors that electronically collect necessary information. Participants will be asked to walk along the walkway and perform various tasks in a single length of the device: (1) complete a normal walk down the walkway; (2) count backwards from 100 by 1; (3) name as many animals as possible; (4) count backwards from 100 by 7; and (5) walk as fast as possible without running down the walkway. A normal walking pace will be gathered using the device prior to the above tasks. This task will be completed at the London (ON, “Canada”) site only and will be conducted in the Brain and Gait laboratory of [name], located at the Parkwood Institute in London, ON, Canada.

### Medication adherence

Participants will be asked to remain on their antidepressant (or other prescribed) medications for the duration of the study. Adherence to this will be determined at each follow-up as participants will be asked if there have been any changes to medication. Information on the medication, dose, frequency, reason, start, and end date of all medications (over-the-counter, prescribed) will be collected.

### Randomization and blinding

After baseline assessments, participants will be randomly assigned to the SSM or HEP arm of the study. Group allocation will be stratified by site (London or Montreal). Additionally, participants will be stratified to the presence of treatment resistance (TR) or not. Stratification and randomization will be conducted by an independent statistician based in London, ON. An independent member from administrative staff at the London site will receive the list of randomization and save it on a secure electronic database with access available to the principal investigator (PI) only if the code needs to be broken in an emergency. This process will ensure that group allocation remains concealed from raters, clinicians and care providers. Due to the nature of the intervention being behavioral in nature, it is not possible to blind participants to study arm assignment.

Participants will be informed by telephone of group allocation by an administrative assistant not involved in the study. Alternatively, participants will be handed a sealed envelope (prepared by the same administrative assistant) by a research assistant.

## Interventions

The interventions will begin after 4–10 eligible participants (per intervention; 8–20 total) have been recruited into the study and have attended a baseline assessment session. Both interventions will require the attendance of 2-h training sessions over four consecutive days. Participants will also attend 1-h follow-up sessions once per week for the remaining 11 weeks and be asked to practice the trained technique at home for 40 min per day. “Practice logs” will be provided to participants to record their daily practice of the trained technique.

### *Sahaj Samadhi* meditation (SSM) – intervention group

This is the experimental arm of the study. It will be delivered at both sites by trained, certified non-clinician instructors available from our collaborative partner, The Art of Living Foundation. During the first day of training, participants will learn the nature of meditation and then have a personal, guided meditation using a mantra, to be brought into their awareness, if the need arises. On days 2–4, there will be a focus on understanding the nature of the mind and the thoughts arising from it, additional guided meditation by the instructor(s), and a discussion of correct/incorrect meditation practices. The first 4 days of training will be 2 h each. Weekly follow-up sessions (1 h) will include 20 min of guided meditation practice. Participants will be trained and be able to discuss with instructors how to respond to the experiences that arise during meditation, what enhances or detracts from effective meditation, and review methods to support meditation at home. The uniqueness of SSM arises from the ultimate goal of quieting the mind until an individual is “aware of awareness.” The goal of SSM is to attain a state of automatic self-transcendence. All SSM participants will be asked to practice SSM at their own homes, twice a day, for the duration of the study. Compliance with this request will be reviewed through assessment of daily practice logs given to all participants.

### Health Enhancement Program (HEP) – active control

The HEP has been designed as a manualized, active control in this study as well as other meditation-based intervention trials. This intervention will allow us to control for several non-specific factors found in a meditation group intervention such as group support/morale, behavioral activation, reduction of stigma, facilitator attention, treatment duration, and time spent on at-home practice. Additionally, we will ensure that HEP matches the time commitment of SSM. The HEP modules will include information sessions on health promotion, healthy diet, self-care, music, and exercise. However, participants will not learn any breathing techniques or meditation. All HEP participants will also be asked to complete daily practice logs. Time commitments to the HEP are identical to those for SSM: 4 days of 2-h training sessions followed by 1-h follow-up sessions for 11 weeks, coupled with 40 min of daily at-home practice.

### Participant adherence to intervention

Daily practice logs will be provided to participants for them to fill out in their own time. Participants will log the days in which they practiced SSM/HEP techniques.

## Statistical analysis

### Sample size

Recruitment is expected to occur over a 26- to 36-month period at a rate of two participants per week (total of *n* = 192). See Fig. 1 for a schematic diagram. It is estimated that a sample of 192 participants will offer sufficient power for the primary outcome (HRSD-17). This sample size calculation is based on an estimated effect size from our pilot data from participants with LLD undergoing SSM or treatment as usual (TAU). Over the 12-week intervention, participants in the SSM group had significant change in HRSD-17 scores when compared to the TAU group (2.66 (95% CI 0.26 to 5.05) point greater reduction; Cohen’s D = 0.61, *p* = .030). Assuming an average cluster size of 4–10 participants and a 1:1 allocation between the SSM and HEP groups, 192 participants will allow us to observe a 2.6-point difference in HRSD-17 scores between the two groups at a two-tailed α = 0.05 and 1 − β = 0.80. A 2.5-point difference is considered to be clinically significant among consensus expert reports and the Food and Drug Administration (FDA) considers it a minimum standard [74]. A 16% rate of attrition for this study is a conservative estimate based on our previously observed 13% attrition rate in the SSM versus the TAU study. As such, it is predicted that approximately 160 of the planned 192 recruited participants will complete the study and we will still have adequate statistical power.

### Primary outcomes

The HRSD-17 scores at baseline, 12-week, and 26-week follow-up of participants assigned to SSM and HEP will be compared using linear mixed models: 2 (SSM vs HEP) × 3 (0 weeks, 12 weeks, 26 weeks). This approach will account for the clustering of observations, since both SSM and HEP will be delivered in a group setting. Next, we will evaluate whether a greater proportion of participants assigned to SSM, compared to HEP, achieve depression remission (defined as a HRSD-17 score ≤ 7 at the 12-week follow-up) using generalized linear mixed models (hypothesis 1B).

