## Methods/Design

### Aims

The objective of this study is to compare the effects of *Sahaj Samadhi* meditation (SSM) on related psychological and biological outcomes against an active control, the Health Enhancement Program (HEP).

Primary outcome: the primary outcome measure will be change in depression scores in the SSM arm compared to HEP at 12 weeks. We will also assess the percentage of SSM participants who will meet the clinical criteria for remission compared to HEP at 12 weeks. Lastly, we will assess whether participants in the SSM arm will continue to have reduced depression scores at the 26-week follow-up.

Secondary outcome: the secondary outcome measure will be a neuropsychological battery for assessing executive function with an emphasis on planning and organization ability, at the primary endpoint of 12 weeks.

Exploratory outcomes: for a complete list of such outcomes and their associated hypotheses, please refer to Table 1.

**Table 1 Tab1:** Objectives and hypotheses

Objective		Hypothesis
Primary		
1.	Using a 12-week RCT, assess whether SSM improves depressive symptoms in LLD compared to an active-control condition; HEP	(a) In participants with LLD, SSM participants, compared to HEP controls, will have a greater reduction in depressive symptoms from baseline to 12-week follow-up, as measured by the Hamilton Rating Scale for Depression (HRSD-17) (b) Compared to HEP, a higher percentage of SSM LLD participants will meet the clinical criteria for remission, as defined by HRSD-17 scores < 8 at the 12-week follow-up
Secondary		
2.	To assess the effects of SSM on a specific executive function, i.e., organization ability in LLD	In participants with LLD, compared to HEP, SSM will be associated with better organization ability, at 12-week follow-up
Exploratory		
3.	To assess the effects of SSM on other executive function domains in LLD	In participants with LLD, compared to HEP, SSM will be associated with better executive functions, at 12-week follow-up
4.	To assess the effects of SSM on global cognition in LLD	In participants with LLD, compared to HEP, SSM will be associated with better global cognition, at 12-week follow-up

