5.	Using magnetic resonance spectroscopy (MRS), assess the effects of SSM on functional connectivity measured by rs-fMRI particularly within the area implicated on the default mode network, volume increase in the bilateral hippocampi and posterior cingulate cortices and levels of glutathione (GSH)	Compared to HEP, SSM will show an increase in functional connectivity especially within the area implicated on the default mode network and also a volume increase in the bilateral hippocampi and posterior cingulate cortices and an increase in levels of GSH in key mood-regulating brain areas (ventro-medial prefrontal cortex)
6.	To investigate whether SSM intervention is associated with sustained improvements in participants’ views of disability (WHODAS 2.0), sleep (Athens Insomnia Scale), quality of life (Euro-QOL), anxiety (Generalized Anxiety Disorder GAD-7, and overall psychological well-being (Ryff’s Scales of Psychological Well-Being; SPWB 9 items) at 12-week follow-up compared to HEP	SSM will be superior to HEP at 12 weeks on all self-rated measures of disability, sleep, quality of life, anxiety, and psychological well-being
7.	To investigate the effects of SSM and HEP on mood and cognition at 26-week follow-up	SSM will continue to be superior to HEP at 26-week follow-up with regard to HRSD-17 scores and executive functioning
8.	To identify and quantify the extent of gait impairment in participants with LLD and explore the effects of SSM intervention on gait impairments at 12 weeks	SSM will be superior to HEP in improving gait measures, including stride length, gait velocity and fear of falling and risk of falling as measured by the Falls Efficacy Scale – International (FES-I) at 12-week follow-up
9.	To explore whether blood inflammation markers, circadian rhythm, and sleep quality (Acti-watch), predict treatment response with SSM	Depression and anxiety symptoms will be associated with levels of inflammatory markers. Levels of inflammatory markers will be decreased, as well as circadian rhythm and sleep quality (Acti-watch) will be improved, in the SSM participants at 12-week follow-up compared to HEP, which in turn will be associated with greater reductions in depression/anxiety scores
10.	To assess participant experience after participating in the interventions (SSM or HEP)	Using the semi-structured McGill Illness Narrative Interview, elucidate what is the participant experience participating in either SSM or HEP?

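### The 2 × 3 mixed model should be tied to the week-12 contrast and should use baseline HRSD-17 and the randomisation strata: an efficiency gain at almost no cost, not a bias

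*Protocol article*

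**What the plan says.** Protocol article, Statistical analysis, Primary outcomes: HRSD-17 scores at baseline, 12 and 26 weeks "will be compared using linear mixed models: 2 (SSM vs HEP) × 3 (0 weeks, 12 weeks, 26 weeks"). The next sentence adds: "This approach will account for the clustering of observations, since both SSM and HEP will be delivered in a group setting". The section then ties the remission analysis to week 12 and to hypothesis 1B. It does not tie the mixed model to hypothesis 1(a) in the same way.

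Aims: "the primary outcome measure will be change in depression scores in the SSM arm compared to HEP at 12 weeks". Hypothesis 1(a) in Table 1 is that SSM participants "will have a greater reduction in depressive symptoms from baseline to 12-week follow-up". Table 1 lists week 26 as exploratory objective 7: "SSM will continue to be superior to HEP at 26-week follow-up with regard to HRSD-17 scores and executive functioning". The Aims text nevertheless mentions week 26 under the primary outcome, and the Background includes persistence to week 26 in the primary hypothesis.

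Randomization and blinding: "Group allocation will be stratified by site (London or Montreal). Additionally, participants will be stratified to the presence of treatment resistance (TR) or not". The same section places randomisation after the baseline assessments. Neither stratum is mentioned in the analysis sections.

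**The concern.** The article gives a model form, and three features of it deserve attention.

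- **Baseline.** With week 0 as one of three response levels and a separate arm effect there, the model estimates a baseline difference that randomisation has already set to zero in expectation. The week-12 contrast then reduces to the difference in mean change, and the information that baseline carries about the week-12 score is not fully used.
- **Target.** An arm-by-time model with three visits yields several possible tests: a week-12 contrast, a week-26 contrast and a joint 2-df test. The Aims make one of these primary, but the analysis section does not say which term delivers it.
- **Strata.** If site or treatment resistance predicts outcome, an analysis without them tends to give a standard error that is too large.

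What is at stake is precision and a fixed primary test. The validity of the comparison is not in question.

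**Working it through.** **The plan's own figure.** Sample size gives 192 randomised, about 160 completers, a 2.6-point difference, two-sided 5% and 80% power. The pilot figures imply SD = 2.66/0.61 = 4.36.

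- Per arm without clustering: 2 × (4.36 × 2.80/2.6)² = 44.2, so 45, or 90 completers. With 16% attrition: 90/0.84, about 108.
- 160/0.84 = 190.5, which agrees with 192 as the attrition step.
- 160 completers then need a design effect of 80/44.2 = 1.81. From 1 + (m − 1) × ICC, that is ICC 0.27, 0.135 or 0.09 for groups of 4, 7 or 10.

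No ICC is stated, so 192 can be neither confirmed nor refuted.

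**Baseline handling, equal SDs, no clustering.** Let ρ be the baseline-to-week-12 correlation. It is not in the article, so 0.3–0.7 is assumed. In units of the common variance:

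- change score: 2(1 − ρ)
- baseline-adjusted or constrained: 1 − ρ²
- ratio: (1 + ρ)/2

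A generalised least squares calculation on the 2 × 3 layout (80 per arm, complete data, SD 4.36 at each visit) returned the same ratios. The last column is the power after adjustment if the change-score analysis had exactly 80%: Φ(2.80/√ratio − 1.96).

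| ρ | Variance ratio | SE, free baseline | SE, constrained | Power, from 80% |
|---|---|---|---|---|
| 0.3 | 0.65 | 0.816 | 0.658 | 93.5% |
| 0.5 | 0.75 | 0.689 | 0.597 | 89.9% |
| 0.7 | 0.85 | 0.534 | 0.492 | 86.0% |

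**Restricted entry.** Participants enter with HRSD-17 between 10 and 22, which may make the baseline SD smaller than the week-12 SD. With k = baseline SD/week-12 SD, the ratio is (1 − ρ²)/(k² + 1 − 2ρk).

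| k (assumed) | ρ = 0.3 | ρ = 0.5 | ρ = 0.7 |
|---|---|---|---|
| 0.75 | 0.818 | 0.923 | 0.995 |
| 0.5 | 0.958 | 1.000 | 0.927 |

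The reduction is then between 0 and 18%. It is never negative, because (k² + 1 − 2ρk) − (1 − ρ²) = (k − ρ)².

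**Clustering.** Group effects that arise during therapy are not removed by a participant's own baseline. As an illustration, split the design effect into a between-group part m × ICC and a within-group part 1 − ICC, and apply the ratio to the second part only.

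- m = 4, ICC 0.27: (1.08 + 0.73 × 0.65)/1.81 = 0.86. With 0.75 in place of 0.65, 0.90.
- m = 10, ICC 0.09: (0.90 + 0.91 × 0.65)/1.81 = 0.82. With 0.75, 0.87.

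So even with equal SDs, the 25–35% gain for ρ of 0.5–0.3 shrinks to about 10–18%, and 80% power becomes about 84–87%.

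**Strata.** Residual variance is multiplied by 1 − R². For assumed R² of 1% to 10%, 80% power becomes 80.4% to 84.0%.

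**Which test.** Suppose the week-12 contrast alone has 80% power, the week-12 and week-26 changes have equal variance, and the two arm contrasts correlate 0.4–0.6 (all assumed). A joint 2-df test then behaves as follows (noncentral chi-square):

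- half the effect left at week 26: 71–72% power
- effect fully maintained: 81–86%
- no week-12 effect, but a week-26 effect that alone would have 80% power: 79–89% rejection

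The last case shows why the term should be named: a joint test can be significant without any week-12 benefit.

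**The case against.** The strongest reply is that this is a condensed article based on an internal protocol that is not shown (Trial status), and a statistical analysis plan may exist. Covariate lists, covariance structure and baseline constraints are commonly left to such documents. That stands for the strata: a reader might infer that the authors decided to leave them out, but the article lists no covariates and excludes none. Leaving them out would in any case be conservative, at a small cost.

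A reader might also infer that the primary test is the 2-df interaction. The article never says so. The expression 2 × 3 describes the factors, and the Aims and hypothesis 1(a) do name the week-12 change. What remains is that the analysis section does not connect its model to that hypothesis. A joint test is also not always weaker, as the fully maintained case shows.

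On baseline, the reply is that a free arm effect at week 0 is only the default reading, and that a change-score contrast matches the declared outcome and is unbiased under randomisation. Both are true. The adjusted contrast targets the same arm difference, however, since expected baseline means are equal by randomisation, and it is at least as precise in large samples.

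**Conclusion.** The point holds as an efficiency and clarity improvement. On its default reading, the stated model gives a valid week-12 comparison that is at most as precise as a baseline-adjusted one, and its link to the primary hypothesis is left unstated.

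The size cannot be fixed from the article, because the correlation, the visit-specific SDs and the ICC are not given. The variance reduction from baseline adjustment is 15–35% under equal SDs without clustering (ρ 0.7–0.3), and about 0–18% if entry restriction compresses the baseline SD to 0.5–0.75 of the week-12 SD. Clustering makes it smaller still. The strata would add little.

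These figures should not be read as showing that the trial is underpowered or its primary analysis biased. They compare two valid analyses and say nothing about whether 192 is enough.

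**What to change.** In Primary outcomes, state that hypothesis 1(a) is tested by the single 1-df SSM–HEP contrast at week 12 from the linear mixed model. Either constrain mean HRSD-17 to be equal across arms at week 0, or model weeks 12 and 26 with baseline HRSD-17 as a covariate. Include site and treatment-resistance status as fixed effects, here and in the remission model. Keep the therapy-group clustering as planned. If a fuller protocol or analysis plan already says this, confirm that it agrees with the article.

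The cost is wording and a few degrees of freedom. HRSD-17 at week 0, site and treatment resistance are all recorded already, and the sample size and visits do not change.

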### Secondary outcomes

Each measure of executive functioning will produce a Z-score from collected data. Z-scores will be compared using linear mixed models: 2 (SSM vs HEP) × 3 (0 weeks, 12 weeks, and 26 weeks). Z-scores for each of the  executive functioning measure will be combined; the mean of the summated Z-scores will then be used to generate an overall Z-score for executive function.

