### Secondary outcomes

#### Rey-Osterrieth Complex Figure

This neuropsychological test asks participants to copy a complex, geometric image by copying it onto a blank piece of paper [49, 50] – the “copy trial.” Participants are then asked to redraw the image from memory after a 30-min delay – the “recall trial.” Although many different scores can be pulled from this assessment, for the purposes of this study we are focusing on those associated with executive functions as assessed by the Boston qualitative scoring system for the Rey-Osterrieth Complex Figure: the “planning” score, the “fragmentation” score, and the “organization” score. The order in which the copied/recalled image is drawn composes the planning score. For example, participants who start with larger, identifiable features (i.e., “configural elements”) score more points than participants who begin their drawing with the details (i.e., “clusters”). The continuity of pen strokes on copied/recalled image drawings creates the fragmentation score. For example, is a line drawn with a single pen stroke or did the participant have to extend the line? The fragmentation and planning scores will be then combined to generate an organization score. Age-scaled norms will be used to create scaled scores for each of these outcomes [51]. Such a scoring method has demonstrated validity among depressed older adults [52].

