### Fidelity/confidentiality

Data will be collected and stored using Research Electronic Data Capture (REDCap), a secure, online data collection tool (access provided by Lawson Health Research Institute in London, ON). Raters will also use REDCap to administer assessments and capture participant data. For assessments that are required to be completed on paper forms (i.e., executive function measures), pertinent data (i.e., Z-scores) will be inputted by the research personnel into REDCap. For assessments that are self-rated, participants will complete a REDCap-generated survey. Collected data will be continually reviewed by the research staff to ensure accuracy of completion. All changes in REDCap will be automatically logged to ensure the fidelity and integrity of the study data. As REDCap is a secure, online data-entry and repository tool, it will be available for access in real time by researchers in both London, ON, and Montreal, QC.

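### The secondary endpoint is organization ability in Table 1, but a battery, separate Z-scores and a composite elsewhere, and nothing says which result tests the stated hypothesis

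*Protocol article*

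**What the plan says.** The protocol article describes the secondary endpoint in four places.

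- **Table 1, secondary objective 2:** "To assess the effects of SSM on a specific executive function, i.e., organization ability in LLD". The hypothesis is that, compared with HEP, "SSM will be associated with better organization ability, at 12-week follow-up".
- **Table 1, exploratory objective 3:** "To assess the effects of SSM on other executive function domains in LLD".
- **Aims, text above Table 1:** "the secondary outcome measure will be a neuropsychological battery for assessing executive function with an emphasis on planning and organization ability", at 12 weeks.
- **Table 2:** the secondary outcome is executive function, with five tests beneath it: Digit Span, Verbal Fluency, CVLT-II Short form, Rey-Osterrieth copy trial and Color Word conditions 1–3.
- **Statistical analysis, Secondary outcomes:** each executive measure yields a Z-score, the Z-scores are compared between arms with linear mixed models, and then "the mean of the summated Z-scores will then be used to generate an overall Z-score for executive function". Organization is not mentioned.

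Table 1 names an ability, not a score, and the test descriptions offer two candidates. For the Rey-Osterrieth figure, "The fragmentation and planning scores will be then combined to generate an organization score". The CVLT-II entry describes semantic clustering as a measure of organization built into that test.

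**The concern.** Four of the five tests in Table 2 would be exploratory if the Rey-Osterrieth score is what Table 1 means by organization, yet Table 2 and the statistical section treat them as secondary. The composite in the statistical section has no hypothesis of its own among the secondary objectives in Table 1. A reader of the final report could not tell from this document whether the secondary hypothesis was met, because an organization result, four other test results and an overall score would all carry the secondary label without any order among them.

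Two things are at stake. First, a favourable result could be picked from an unranked set after the data are seen. Second, organization alone and the composite can differ greatly in power, so the choice between them can decide whether the secondary hypothesis is reported as supported.

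**Working it through.** **No plan figure to reproduce.** The sample size section gives power for HRSD-17 only. Nothing is stated for the secondary endpoint, so the figures below rest on labelled assumptions.

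**Step 1. Status of each result, by place.**

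| Place | Organization | Other executive tests | Composite |
|---|---|---|---|
| Table 1 | Secondary, the only one | Exploratory | Not mentioned |
| Aims text | Emphasised part of a battery | Secondary, within the battery | Not mentioned |
| Table 2 | Not separated | Secondary | Not mentioned |
| Statistical analysis | Not mentioned | Secondary, one Z-score per measure | Secondary |

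The rows cannot all be followed at once.

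**Step 2. Number of tests.** One Z-score for each of the five tests in Table 2, plus the composite, gives six. Several tests produce more than one score, so six is a lower count.

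**Step 3. False-positive chance with no true effect.** Assumptions: five jointly normal test statistics with common correlation ρ (not in the document), a composite statistic equal to their mean divided by √((1+4ρ)/5), and each tested two-sided at 0.05. A simulation with 400,000 draws gives:

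| ρ | Any of five tests or composite | Organization or composite only |
|---|---|---|
| 0 | 24.3% | 9.2% |
| 0.3 | 21.4% | 8.6% |
| 0.5 | 18.4% | 8.0% |
| 0.6 | 16.8% | 7.6% |

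Hand check at ρ = 0: five tests alone give 1 − 0.95⁵ = 22.6%, and the composite adds a little. These chances count a significant difference in either direction. Counting only those that favour SSM, the chance cannot exceed 6 × 0.025 = 15%.

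**Step 4. Power of organization alone against the composite.** Inputs: about 160 completers (sample size section), so 160/2 = 80 per arm. Assumed: d = 0.5 on organization, ρ from 0.2 to 0.5, equal weights (read from the word mean), no clustering. Power = Φ(d√(80/2) − 1.96), with √40 = 6.325.

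- Organization alone: Φ(0.5 × 6.325 − 1.96) = Φ(1.20) = 89%.
- Composite, only organization responds: d = (0.5/5)/√((1+4ρ)/5). At ρ = 0.2, d = 0.167 and power is 18%. At ρ = 0.5, d = 0.129 and power is 13%.
- Composite, all five respond equally: d = 0.5 × √(5/(1+4ρ)). At ρ = 0.2, d = 0.83 and power exceeds 99%. At ρ = 0.5, d = 0.65 and power is 98%.

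**Step 5. Break-even.** Let q be the average effect on the other four tests as a share of the organization effect. The composite matches organization alone when q = (√(5(1+4ρ)) − 1)/4. That is (3 − 1)/4 = 0.50 at ρ = 0.2 and (3.873 − 1)/4 = 0.72 at ρ = 0.5. Below that share the composite loses power; above it, it gains.

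**The case against.** The strongest reply is that the statistical section does not replace organization with a composite. It compares each measure's Z-score first and adds the overall score afterwards, so organization can still be tested separately. Ordering of secondary tests is also commonly left to a statistical analysis plan, which is not shown. The first part stands: a reader might infer that the composite swamps the stated hypothesis, but the text keeps the separate tests, and exploratory objective 3 predicts benefit in other domains too, a pattern in which the composite may gain power. The second part stands only in part. A separate plan could choose one version, but the chosen version would still contradict another part of this document.

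Three further inferences are tempting and are not supported.

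- **Organization is counted twice in the composite**, because it is built from planning and fragmentation. This would need all three scores to enter, and the statistical section gives each measure a single Z-score.
- **The composite cannot be rebuilt from the database.** The confidentiality section says "pertinent data (i.e., Z-scores) will be inputted by the research personnel into REDCap", and a mean of stored Z-scores can be recomputed. Only re-deriving each Z-score from raw data would need the paper forms.
- **Z-scores from collected data conflict with the norm-based scaling described per test.** Norm-scaled scores are also derived from collected data and can be expressed as Z-scores. The reference population is unstated, which is a detail and not a contradiction.

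**Conclusion.** The concern holds as an inconsistency in the definition and rank of the secondary endpoint. The same executive tests are exploratory in one place and secondary in others, and no passage says which result answers the Table 1 hypothesis. Used without ranking, the six tests carry about a 17% to 24% chance of at least one false positive, for assumed correlations of 0.6 down to 0.

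The documents do not support a claim that the composite necessarily costs power. The drop from 89% to 13–18% requires the other four tests not to respond at all; with equal response the composite reaches at least 98%. All of these figures rest on the assumed d = 0.5, a common correlation and no clustering. The spread between the two patterns is itself the reason to fix the endpoint in advance. The primary HRSD-17 analysis is unaffected, so this should be corrected but does not threaten the main result.

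**What to change.** In the Aims (text and Table 1), Table 2 and the statistical section on secondary outcomes, name one organization measure at week 12 as the single secondary endpoint that tests the Table 1 hypothesis. The Rey-Osterrieth organization score is a natural example, since the article derives a score of that name; CVLT-II semantic clustering is the other candidate, and the choice is the sponsor's. Label the remaining tests and the composite exploratory or supportive in all three places. Recruitment has begun, so the change should be dated and made before outcomes are compared by arm.

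The cost is wording in three places. The price in inference is that a broad cognitive benefit, which the composite might detect better, would count only as supportive evidence. Entering raw test scores in REDCap alongside the Z-scores would make the scoring easier to check, but it is optional.
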